### Statistical analysis

**
*Sample size*
**

A formal sample size calculation was not conceivable due to lack of preliminary data regarding metformin and leprosy. Because of limitations in feasibility and allocated budget, the target sample size will be 150 participants (75 per arm). To account for up to 10% lost-to-follow-up, the sample size is increased to 166 participants. If we assume that 50% of participants in the standard-of-care (control) arm will develop a T1R/T2R during the 48 weeks study follow-up
^
4
^, a sample size of 75 participants per arm, achieves 89% power at a 2-sided 0.05 significance level, based on an estimated intervention effect of 50% relative risk reduction.

**
*Analysis of the primary efficacy and safety endpoints*
**

The primary analysis will be intention-to-treat containing all randomized participants. In addition, the primary outcomes will be analysed in the per-protocol population, which will exclude participants with a final diagnosis other than MB leprosy, did not adhere to in- or exclusion criteria or major protocol violations, namely:

•     Participants who took <80% of the allocated doses of the IMP during the intervention period of 24 weeks based on the registered pill counts on pharmacy records, and/or

•     Participants who missed more than 14 consecutive daily dosages of the IMP during the intervention period of 24 weeks.

Due to potential non-adherence to the IMP, we will analyse risk-factors for non-adherence.

The primary efficacy outcome is the proportion of participants experiencing a LR during study follow up (total 48 weeks). The effect measure is the treatment difference between the intervention (metformin plus MDT) and control (placebo plus MDT) group. The treatment difference will be quantified in a logistic regression model that includes BI as a continuous variable and study site. Results will be marginalized over BI and study site. We will also consider a model using a log-link, which provides risk ratios. If loss to follow-up is 5% or more, we will take censored data into account and fit the model using pseudo-values. The heterogeneity of the treatment effect will be assessed by including an interaction term between treatment and BI, as well as between treatment and study site (two separate models). For the safety outcome, the proportion of participants with at least one AE within the first 24 weeks will be compared. The chi-squared test will be used to compare the treatment arms, or Fisher’s exact test in case the expected number under the null hypothesis in at least one of the cells is smaller than one. The analyses to be performed will be documented in the Statistical Analysis Plan (SAP), which will be finalized before the database is unlocked and the final analysis with the unblinded data is performed. R software will be used.

**
*Analysis of the secondary outcomes*
**

For all secondary outcomes, we make a comparison correcting for BI and study site, except for those related to (S)AE (i.e. outcome 4 and 5). Outcomes 1, 4 and 7 are analyzed in the same way as the two primary outcomes. For time to first LR, we compute and plot Kaplan-Meier curves by treatment arm and fit Cox proportional hazards models that include BI and study site. Although the value of the hazard ratio cannot be given a causal interpretation, we include this model because it is the standard approach in time-to-event analyses. However, we will also perform an analysis using restricted mean survival time as outcome. Severity of T1R and T2R at onset will be compared with a regression model that is determined based on the distribution of the scores. The total number of AEs within the intervention period will be compared via a quasi-Poisson regression model. Cumulative corticosteroid usage is modelled via linear regression. For the participants that are still using corticosteroids at 48 weeks, values will be treated as right censored. If needed, we will use the Box-Cox procedure to determine an appropriate transformation. We will allow for extra values at zero via a zero-inflated model, in case some of the participants with a mild reaction do not receive corticosteroids. Quality of life is compared over the four time points using mixed effects models. If the distribution in QoL is too skewed, we will use beta regression using generalized estimating equations to correct for correlation within individuals.

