### Outcomes

**
*Primary efficacy outcome*
**

The proportion of participants experiencing a LR during study follow-up (total 48 weeks).

**
*Primary safety outcome*
**

The proportion of participants with at least one adverse event (AE) within the first 24 weeks of the study.

**
*Secondary outcomes*
**

1.   The proportion of participants experiencing a T1R or T2R (as separate outcomes) at 24 and 48 weeks.

2.   Time to first LR and time to first T1R and T2R as separate outcomes, over the full 48 weeks.

3.   Severity of T1R and T2R at onset based on investigator-assessed validated Clinical Severity Scores
^
52,
53
^.

4.   The proportion of participants with at least one SAE within the first 24 weeks of the trial.

5.   The total number of AE within the first 24 weeks of the trial.

6.   Cumulative corticosteroid usage in participants with a leprosy reaction.

7.   The proportion of participants experiencing clinical nerve function impairment (NFI) developed over the full 48 weeks.

8.   Quality of Life (QoL) at enrolment, half-way treatment intervention (12 weeks), end of treatment intervention (24 weeks), and end of study (48 weeks) using validated local language versions of the Dermatology Life Quality Index (DLQI) and the 36-item Short Form Survey (SF-36).

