### Randomisation and treatment allocation

**
*Randomisation*
**

All participants who present with newly diagnosed MB leprosy and agree to participate in the trial, will be screened for eligibility. Participants eligible for enrolment, will be randomized to two parallel groups in a 1:1 ratio: metformin for 24 weeks versus identical placebo for 24 weeks. Placebo will be identical in appearance to active drug and contain the inactive ingredients sodium carboxymethyl cellulose, hypromellose and magnesium stearate. It will be dosed and dispensed in the same way as metformin. Randomization will be stratified by BI-score (BI ≥ or < 4) and study site. The randomization list will be computer-generated based on random permuted blocks with variable block size. The randomization list will be generated through a statistical code and securely incorporated within the trial database. Based on the randomization list blinded drug packages (treatment packs are labelled with a different code per site) are distributed to all study sites. A 24h web-based randomization service is provided through
REDCap. Treatment should start as soon as possible after randomization. Unblinding will be performed after the data collection, statistical analysis plan and statistical coding have been completed, or earlier at the individual level, if this is essential for best management of the participant and agreed upon by the Site Principal Investigator (PI) and Chief Investigators. Study medication must be discontinued for an individual after unblinding. All instances of unblinding should be reported to the Data Monitoring Committee (DMC).

**
*Blinding*
**

Identical vials of metformin or placebo tablets will be prepared by the Trial Pharmacist at OUCRU ID’s Clinical Trial Unit. The Trial Pharmacist will make up and label individual-participant blinded treatment packs with trial numbers, containing either active drugs or identical placebo sufficient for 6 periods of 4 weeks of treatment according to the prespecified randomization list. No other study team members including PI, study coordinators and site PI’s, doctors, nurses, laboratory technician’s and pharmacist’s have access to the key of the randomization list.

**
*Treatment discontinuation*
**

The participants may request for any reason to withdraw consent for treatment or the investigator may discontinue treatment for any of the following reasons:

An AE which requires discontinuation of the investigational medicinal product (IMP,

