Table 1).Pregnancy confirmed by urine dipstick for human chorionic gonadotrophin hormone.Request of clinical team if believed the IMP is no longer in the best interest of the patient.

**Table 1. T1:** Overview of adverse events that require discontinuation of Investigational Medicinal Product.

Adverse events
• Severe acute renal impairment (estimated glomerular filtration rate (30mL/min/1.73m ^2^)
• Lactate ≥ 3 mmol/L and/or onset of metformin-related lactic acidosis (testing triggered in case of clinical suspicion)
• Severe liver involvement: alanine transaminase (ALT) > 3x upper limit normal (ULN), if suspected metformin-associated, or ALT > 4x ULN
• Hypoglycaemic episode (blood sugar < 3.9 mmol/L OR < 70 mg/dL)
• Severe diarrhoea (≥ 5 stools/day with signs of dehydration)
• Mild/moderate diarrhoea, vomiting and/or epigastric pain, if persistent and patient is uncomfortable (despite dose reduction)

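### The supplementary per-protocol analysis of the adverse-event outcome removes participants because of the event itself, so it tends to understate harm in the arm with more AE-driven stops

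*Protocol article*

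**What the plan says.** All references are to the protocol article. Under *Statistical analysis*, subsection *Analysis of the primary efficacy and safety endpoints*, the main analysis set is fixed first: "The primary analysis will be intention-to-treat containing all randomized participants". The next sentence adds the second set: "In addition, the primary outcomes will be analysed in the per-protocol population". *Outcomes* lists two primary outcomes. The efficacy outcome is the proportion with an LR over 48 weeks. The safety outcome is: "The proportion of participants with at least one adverse event (AE) within the first 24 weeks of the study".

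The per-protocol set excludes major protocol violations, which are spelled out as two adherence rules joined by and/or:

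- "Participants who took <80% of the allocated doses of the IMP during the intervention period of 24 weeks", judged from pill counts;
- "Participants who missed more than 14 consecutive daily dosages of the IMP during the intervention period of 24 weeks".

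Neither rule exempts stops that the protocol itself requires, and neither ends the adherence count at the first LR.

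Table 1, under *Randomisation and treatment allocation*, is titled "Overview of adverse events that require discontinuation of Investigational Medicinal Product". It covers renal, lactate, liver, hypoglycaemic and severe or persistent gastrointestinal events. An LR is not on the list.

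*Analysis of the secondary outcomes* says that outcome 4 (at least one SAE) follows the approach used for the primary outcomes. This could be read as carrying the per-protocol set over to SAEs.

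**The concern.** The per-protocol set is defined by something that the safety outcome causes. An AE of the Table 1 kind leads to a stop, the stop produces missed doses, and the missed doses remove the participant. Each person removed this way has, by definition, had the outcome being counted. The remaining AE proportion is too low in both arms, and more so in the arm with more AE-driven stops. If metformin causes such stops, the per-protocol comparison moves towards no difference exactly when there is harm to see.

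The trial is meant to establish tolerability and safety and to inform a Phase 3 trial. A prespecified per-protocol AE result placed beside the intention-to-treat result could be quoted as reassurance that it cannot give.

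A related but weaker question concerns efficacy. Doses missed after an LR count against adherence, so an early LR followed by a stop would be deleted together with the participant.

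**Working it through.** **Plan's own figure.** The article gives no figure for the per-protocol analyses. Its planning rates do reproduce: 75 per arm, 50% vs 25% with an LR and two-sided 0.05 give 89.3% power (stated: 89%). I use 50% and 25% below.

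**When a stop leads to exclusion.** Dosing lasts 24 × 7 = 168 days.

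- Last dose on day 153: 168 − 153 = 15 consecutive doses missed, which is more than 14, so excluded.
- Last dose on day 154: 14 missed, so not excluded by this rule.
- The 80% rule corresponds to 0.8 × 168 = 134.4 days. For a permanent stop, the consecutive-dose rule therefore catches more people.

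Only stops in roughly the last two weeks of dosing escape.

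**Safety.** Let p be the true AE proportion in an arm and s the share of the arm that stops for an AE and is excluded. Everyone in s had an AE, so the per-protocol proportion is (p − s)/(1 − s). Any other exclusions are taken as unrelated to AE status. Assumed rates are p = 30% metformin vs 20% placebo, a true excess of 10 points.

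| Stops for AE (metformin vs placebo) | Metformin | Placebo | Difference |
|---|---|---|---|
| 2% vs 0% | 0.28/0.98 = 28.6% | 20.0% | 8.6 points |
| 5% vs 1% | 0.25/0.95 = 26.3% | 0.19/0.99 = 19.2% | 7.1 points |
| 10% vs 2% | 0.20/0.90 = 22.2% | 0.18/0.98 = 18.4% | 3.9 points |
| 10% vs 1% | 0.20/0.90 = 22.2% | 0.19/0.99 = 19.2% | 3.0 points |

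With 166 randomised, an arm has 83 participants. So 2%, 5% and 10% are about 2, 4 and 8 people.

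**Efficacy.** Let e be the share of LRs that fall within the 24 weeks and q the share of those that lead to exclusion. Then x = p·e·q, and the per-protocol risk is (p − x)/(1 − x). The Introduction says only that most reactions occur in the first six months; e = 60–80% and every q are assumptions.

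- q = 0: no bias.
- No true effect, equal q: risk ratio (RR) 1.00.
- True RR 0.50, equal q of 10–30%: RR 0.49 to 0.47.
- No true effect, e = 0.8, q = 30% metformin vs 10% placebo: (0.50 − 0.12)/0.88 = 43.2% vs (0.50 − 0.04)/0.96 = 47.9%, RR 0.90. With the two q swapped, RR 1.11.
- True RR 0.50, e = 0.8, same unequal q: RR 0.42, or 0.54 when swapped.

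**Would counting adherence only to the first LR cure this?** Not entirely. Assume 50% LR in both arms, 70% of these spread evenly over the 24 weeks, chance non-adherence of 20% vs 10% by arm, and non-adherence proportional to time observed. Early-LR participants are then observed for half the period on average.

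- 20% arm: LRs kept 0.35 × 0.90 + 0.15 × 0.80 = 0.435; others kept 0.50 × 0.80 = 0.400; 0.435/0.835 = 52.1%.
- 10% arm: LRs kept 0.35 × 0.95 + 0.15 × 0.90 = 0.4675; others kept 0.50 × 0.90 = 0.450; 0.4675/0.9175 = 51.0%.

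Both exceed the true 50%, because LRs are now kept preferentially.

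**The case against.** The strongest reply is that nothing primary is affected. Intention-to-treat in all randomised participants comes first for both outcomes, so everyone who stopped for an AE stays in the main safety comparison. SAEs and the total AE count are separate secondary outcomes, and an independent committee sees unblinded data. This stands. A reader might infer that the trial's safety conclusion is biased or that harm will be concealed; the article does not support that.

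A reader might also infer that per-protocol efficacy is biased in favour of metformin. That does not follow. No rule makes an LR a reason to stop IMP. The routes left are a clinical-team request or the participant's own decision. The trial is double-blind, and the article gives no reason to expect stopping after an LR to differ by arm. With equal stopping there is no bias under the null, and with unequal stopping the sign depends on which arm stops more.

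The stop rates may also be low. *Adverse events and safety reporting* expects about 10% gastrointestinal side-effects on metformin, mostly mild and passing. This is why a range is shown, and at its lower end the distortion is small.

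Finally, whether a required stop counts as missed doses could be left to the SAP. That has some force, but the 80% rule refers to all allocated doses over 24 weeks and is judged by pill count, which takes no account of the reason for stopping. Sending the safety outcome to this set is stated in the article itself.

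**Conclusion.** The safety point holds for the supplementary analysis. As written, the per-protocol AE comparison is selected on a consequence of its own outcome and tends to understate harm in the arm with more AE-driven stops. Under the assumed 30% vs 20%, between 8.6 and 3.0 of the 10 points remain. The size rests entirely on assumed AE and stop rates; the direction follows from the exclusion rules together with Table 1. Severity is moderate to minor, because the intention-to-treat safety result is untouched.

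For efficacy the conclusion is conditional: the per-protocol estimate can be biased, in an unknown direction, if LRs lead to stopping IMP at different rates by arm.

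**What to change.** 1. Limit the per-protocol analysis to the efficacy outcome. State that AEs and SAEs are analysed only in all randomised participants, or in all who took at least one IMP dose. This takes one or two sentences in the protocol and SAP and needs no new data. The article reports enrolment as ongoing and the SAP as due before the unblinded analysis, so the change can be made before results are known.

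2. For per-protocol efficacy, state the caveat that adherence is counted after the first LR and report IMP stops following an LR by arm. Alternatively, add a sensitivity analysis that counts adherence only up to the first LR. Its costs are cutting the dose records at the LR date and a selection of its own, since participants with an early LR have less time to become non-adherent. It should therefore sit beside the stated definition and not replace it.

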### Leprosy reactions

The clinical management of leprosy is complicated by immune-mediated reactions, i.e. unpredictable episodes of exacerbated inflammation occurring before, during or after multi-drug therapy, affecting around 30–50% of people with MB leprosy
^
3
^. The majority of reactions occur during the first six months after treatment has been initiated
^
4–
7
^. Leprosy reactions (LR) are the most important cause of irreversible nerve damage leading to anatomical deformities and disabilities, imposing a physical, social and financial burden on people affected by leprosy and their households
^
8–
10
^. Two distinct LR exist: Type 1 (T1R) or reversal reactions, a delayed hypersensitivity reaction mostly occurring in the borderline forms of leprosy; and Type 2 (T2R), known as erythema nodosum leprosum, which is believed to result from immune-complex deposition and occurs in borderline lepromatous and lepromatous leprosy
^
11
^. T1R is characterised by acute inflammation and swelling of pre-existing skin lesions, oedema of extremities and face, neuritis, and infrequently systemic symptoms
^
12
^. T2R is a multisystem disease characterized by the sudden onset of painful, erythematous, subcutaneous skin lesions symmetrically distributed on face and extremities, are not related to the existing leprosy lesions and are usually accompanied by fever, neuritis, arthritis, orchitis, iridocyclitis and nephritis
^
13,
14
^.

The immunopathogenesis of LR remains poorly understood. The bactericidal effect of MDT creates a reservoir of bacterial breakdown products, which are recognized by the innate immune response and cause migration of pro-inflammatory cytokines and CD4+ T-cells to the site of infection. Activated CD8+ T-cells destroy the
*M. leprae*-infected Schwann cells leading to nerve damage. Although the clinical presentation of T1R and T2R are distinct, it is suggested that both reactions share aspects of their immunopathogenesis including enhanced Th1 responses to
*M. leprae* and macrophage activation reflected by increased levels of similar pro-inflammatory cytokines, such as IFN-γ and TNF-α,IL-1β and IL-6
^
11
^. In T1R, immunological markers like IP-10 and acute phase proteins such as CRP are substantially elevated during the reaction
^
11,
15
^. In T2R T-cell dysregulation with increased CD4+/CD8+ ratio and reduced numbers of Tregs play a key role, tipping the balance towards pro-inflammation
^
16–
18
^.

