LR are a major clinical challenge as they are often chronic, recurrent and require long-term use of potent immunosuppressant’s. Oral corticosteroids remain the first-line therapy of LR although 40% of people with T1R show no clinical improvement
^
5,
19
^. Prolonged high dose corticosteroids are often necessary, causing serious adverse effects (SAE, i.e. peptic ulcer, diabetes mellitus, osteoporosis) and even death
^
20,
21
^. There is a great need to improve treatment strategies and design efficacious, safe and affordable interventions to prevent or limit the development of LR and subsequent neurological impairments and to further elucidate its immunopathogenesis.

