### Data collection

Participants will be enrolled in the trial for a total of 48 weeks. Treatment with metformin or placebo (IMP) is the only intervention used in the MetLep Trial. During the first two weeks, adjunctive metformin hydrochloride 500mg extended-release tablets or matched placebo will be given once daily, escalating to 1000mg metformin hydrochloride extended-release tablets or placebo once daily for another 22 weeks, in addition to standard-of-care MDT. The total duration of IMP intervention will be 24 weeks, while the total duration of MDT will be 48 weeks complying to WHO and national guidelines (
Figure 1). Appropriately trained clinicians and/or nurses with experience in the management of leprosy will be responsible for clinical care. In principle, participants will be reviewed every four weeks (accumulating to a total of 15 visits spread over 48 weeks) to assess the response to treatment, the development of LR and other outcome measures (more details in
Table 2). Home visits may be used to minimise inconvenience for participants. In case of clinical deterioration (i.e. adverse events, LR), additional unscheduled visits may occur. Study participants who develop a LR will receive appropriate anti-inflammatory treatment according to national guidelines. Participants who miss follow-up visits will be contacted by phone. Clinical and laboratory data (including AEs) will be entered into an electronic REDCap database hosted by OUCRU ID. REDCap is a secure, web-based application designed to support data capture for research providing audit trails for tracking data manipulation.

**Table 2. T2:** Schedule of clinical procedures and laboratory investigations.

	**Screening**	**W0** **Enrolment**	**W2**	**W4**	**W8**	**W12**	**W16**	**W20**	**W24**	**W28**	**W32**	**W36**	**W40**	**W44**	**W48** **Completion of MDT**	**LR (Any time point)**	**Minimum number of visits**
**Visit no**	V00	V01	V02	V03	V04	V05	V06	V07	V08	V09	V10	V11	V12	V13	V14	VLR	15
Patient information and informed consent	X																1
Registration Study ID	X																1
Eligibility criteria assessment	X																1
Randomisation		X															1
Initiation IMP		X															1
Increase dosage IMP			X														1

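### Secondary outcome 6 has no time window, and right-censoring the steroid total at week 48 makes the censoring informative; an arm with later reactions is likely, not certain, to look worse than it is

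*Protocol article*

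**What the plan says.** In the Outcomes section of the protocol article, secondary outcome 6 is "Cumulative corticosteroid usage in participants with a leprosy reaction". No period is attached, whereas outcomes 1, 2, 4, 5 and 7 each name 24 or 48 weeks.

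Under Analysis of the secondary outcomes: "Cumulative corticosteroid usage is modelled via linear regression", and then "For the participants that are still using corticosteroids at 48 weeks, values will be treated as right censored". A Box-Cox transformation and a zero-inflated model are held in reserve. The covariates are those used throughout: "For all secondary outcomes, we make a comparison correcting for BI and study site".

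The timing is fixed under Data collection: "Participants will be enrolled in the trial for a total of 48 weeks" and "The total duration of IMP intervention will be 24 weeks". The clock therefore runs from enrolment and not from the reaction. The introduction (Leprosy reactions) says "The majority of reactions occur during the first six months after treatment has been initiated" and "Prolonged high dose corticosteroids are often necessary". It gives no steroid dose, course length or spread, and reactions are treated according to national guidelines.

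**The concern.** Two things are wrong with the rule as written.

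First, it implies a target that the plan does not name. For a participant who completes week 48, the dose taken during the study is known. It counts as censored only if the target is the total over the whole course, part of which falls after the trial ends.

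Second, even for that target, censored linear regression needs the censoring value to be independent of the total, given the covariates. Follow-up ends at a fixed time, and the dose reached by then depends on how fast the participant accumulates it. The same problem is familiar from censored costs. Adjustment for BI and site would not be expected to remove it.

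The consequence for the comparison depends on onset. A participant who reacts later has less time to finish a course before week 48 and is more likely to be censored. Time to first reaction is itself a secondary outcome, and study drug stops halfway through follow-up, so a difference in onset between arms is possible. Reduced steroid exposure is one of the benefits the protocol hopes for, so the direction of error matters.

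**Working it through.** **No figure to reproduce.** The protocol gives no assumed value, effect or precision for this outcome. Dose, course length, spread and delay below are assumptions. Only the 48-week limit, the concentration of reactions in the first six months and the reaction rates come from the document.

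**Algebra.** Let R be the dose rate, D the course length and S the week of onset, so that A = 48 − S is the time available.

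- Flat dosing: total T = R × D; censoring value C = R × A. If R, D and S are independent, Cov(log T, log C) = Var(log R). With a log-SD of 0.5 this is 0.5² = 0.25. It is zero only if everyone has the same rate.
- Dose declining linearly to zero over the course: T = R × D / 2; C = R × (A − A²/(2D)). C now contains D as well, so T and C are dependent even when R is constant.

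**Illustration.** Two participants start at week 32 (A = 48 − 32 = 16) with 24-week courses at flat rates r and 2r. Their totals are 24r and 48r, and they are censored at 16r and 32r. The model treats the first as exchangeable with everyone whose total exceeds 16r, including people at twice the rate. The unobserved remainder is therefore pushed too high.

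**Simulation.** 60,000 reactors per arm; control onset uniform over weeks 0 to 24; log-normal dose rate and course length. The only difference between arms is later onset in one, so the true contrast in full-course dose is zero. A normal model with right censoring is fitted to the log total. Entries are the log-scale estimate for the later arm; the range runs from flat to declining dosing.

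| Median course | Log-SDs (rate, course) | 8 weeks later | 12 weeks later |
|---|---|---|---|
| 24 weeks | 0.5, 0.5 | +0.06 to +0.12 | +0.11 to +0.21 |
| 20 weeks | 0.5, 0.5 | +0.04 to +0.08 | +0.08 to +0.17 |
| 20 weeks | 0.4, 0.4 | +0.03 to +0.07 | +0.06 to +0.13 |
| 12 weeks | 0.4, 0.4 | about +0.01 | +0.02 to +0.03 |

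In the first row with a 12-week delay, 24% of control and 53% of later-arm reactors are censored. In the third row it is 10% and 39%.

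The rows with log-SD 0.5 and courses of 20 to 24 weeks span +0.04 to +0.21. As ratios, exp(0.04) = 1.04 and exp(0.21) = 1.23, that is, 4% to 23% too high.

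**Where it vanishes or reverses.**

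- No delay: about 0.
- Almost no spread in dose rate, flat dosing: about 0. With declining dosing a bias remains (about +0.06; 24-week course, 8 weeks later).
- Little spread in rate, negatively correlated with duration: −0.003 to −0.015.
- Dose rising over the course (20-week course, 12 weeks later): −0.05 with no spread in rate, 0.00 at log-SD 0.4, +0.05 at log-SD 0.6.

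**At trial size.** Under the protocol's own assumptions (75 per arm, 50% reacting on control, 50% relative reduction), reactors number 75 × 0.50 = 37.5, about 38, and 75 × 0.25 = 18.75, about 19. With a 20-week course, log-SDs of 0.4 and a 12-week delay, the mean bias is +0.07 (flat) to +0.13 (declining), against an SD of the estimate of 0.18 to 0.20.

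**Contrast in dose actually taken to week 48.** In the third-row scenario with a 12-week delay, the later arm is at −0.12 (flat) or −0.04 (declining), where the censored model gives +0.06 or +0.13. Across the runs with 20-to-24-week courses and 8-to-12-week delays the 48-week contrast lies between about −0.02 and −0.18.

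**The case against.** The best defence is that the plan has noticed a real problem. With no window on outcome 6, censoring use that is ongoing at week 48 implies a whole-course target, and for that target those participants are incompletely observed. Counting their totals as complete would also be wrong. This stands: one might infer that nothing is censored at week 48, but that is true only once the target is defined as use within 48 weeks. What remains is that the target is unstated and the technique does not suit the one it implies.

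The second objection is that the size rests on inputs the document does not supply. That also stands. The protocol's stated effect is fewer reactions, not later ones, and most reactions are expected in the first six months. If courses are short, few totals are censored and the bias is negligible.

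The third is that dose to week 48 has its own distortion. Later reactors have less time to accumulate dose, so that contrast flatters them by an amount similar to the bias criticised here. This stands as a downside to be declared. The difference is that use within 48 weeks is a defined and observed quantity, read as such.

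A reader might go further and infer that a beneficial delay on metformin will be reported as harm. The documents do not support this: they contain no evidence of a delay, the direction depends on the dosing pattern, and in about 38 versus 19 reactors the bias is smaller than chance variation.

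**Conclusion.** The point holds in a limited form. The protocol fixes a rule whose target is unstated and whose independence assumption fails whenever dose rates differ between participants or decline over the course. That follows from the algebra and needs no assumed figures.

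Direction and size do need assumptions. If one arm reacts later, overestimation of its steroid use is likely but not certain. It is roughly 4% to 23% with median courses of 20 to 24 weeks, log-SDs of 0.5 and a delay of 8 to 12 weeks. It is close to zero with short courses, uniform flat dosing or no delay, and could be negative with back-loaded use. At the expected number of reactors it is about 0.4 to 0.6 of the SD of the estimate (0.07/0.18 and 0.13/0.20).

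This is one of eight secondary outcomes; the primary efficacy and safety analyses are untouched. The rule should be changed because the correction is cheap and can be made before unblinding.

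**What to change.** Define outcome 6 as the corticosteroid dose taken from randomisation to week 48. Use the observed total, without censoring, for every participant who completes week 48, including those still on steroids. Treat only loss to follow-up before week 48 as missing, handled by inverse-probability weighting or multiple imputation. Report the proportion still on steroids at week 48 by arm beside it.

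State the limitation with the result: later reactors have less time to accumulate dose, so the contrast describes use within 48 weeks and not full-course dose.

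If full-course dose is the intended target, say so, and replace censored regression on the dose scale by a method that handles censoring on the time scale. One example is inverse-probability-of-censoring weighting over a fixed window after onset.

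The cost of the first option is about two sentences in the protocol and SAP and a simpler model. It gives up any statement about steroid use after week 48, which the trial does not observe. The protocol says the SAP will be finalised before the final unblinded analysis, so the change can be made there.
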